## **6.6 Compliance Assessment**

Investigational product compliance shall be examined by the investigator in comparison of residual amount of investigational product brought by the subject upon every visit. Residual amount after administration must be returned to the pharmacy and recorded on dispense records. Remaining quantity after administration of rescue drug must also be returned to the pharmacy and recorded on dispense records.

$$\text{Drug compliance (\%)} = \frac{\text{Number of actual administrations}}{\text{Number of scheduled administrations}} \times 100$$

\*Number of scheduled administrations: It is calculated by the number of administrations scheduled between the night of visit 2 or 3 and the morning of next visit.

## **6.7 Co-administered Drugs and Treatment**

### **6.7.1 Permitted Drugs**

Following drugs can be co-administered during clinical trial period.

- 1) Rescue drug (Acetaminophen below dosage of 1,950 mg per day) but administration 24 hours prior to visit is prohibited
- 2) Low dosage aspirin (Maximum daily dosage of 200mg) administered for prevention of cardiovascular disease must be administered without change in dosage until completion of clinical trial. However, administration 24 hours prior to visit is prohibited.
- 3) Co-administered drugs which were administered to the subject prior to participation in this clinical trial deemed to not impact the interpretation of

study results are permitted by decision of clinical trial physician.

- 4) Stomach system related drugs such as proton pump inhibitor and H2-blocker can be administered with prescription when adverse events related to stomach system occur or by decision of clinical trial physician.
- 5) Other drugs used daily for purpose of treatment for other disease and adverse events must be co-administered through consultation with attending physician.

Information(Name, purpose, dosage, administration period, etc.) on all drugs administered(Includes drugs for treatment of other disease and adverse events) shall be recorded in detail in case report for subject.

### **6.7.2 Restricted Drugs**

Following drugs are restricted from co-administration during clinical trial period.

- 1) Surgical intervention
- 2) Steroid injection in glenoid cavity, orally administered steroid, hyaluronic acid injection
- 3) Muscle relaxant
- 4) Physical therapy and oriental therapy(Acupuncture, cupping, moxibustion) for pain relief, chiropractic therapy
- 5) Study drug, pain reliever excluding rescue drug, anti-inflammatory pain reliever(Locally spread solvent, patch included)
- 6) Psychoactive drug, narcotic analgesic, anticonvulsant
- 7) Sulfonylurea hypoglycemic agent(Tolbutamide, etc.) and new quinolone antibiotics(Enoxacin, etc.)
- 8) ACE inhibitor
- 9) Aspirin(When daily dosage exceeds 200mg)
- 10) Furosemide and thiazide diuretic(Hydrochlorothiazide, etc.)
- 11) Lithium
- 12) Methotrexate
- 13) Coumarin anticoagulant(Warfarin, etc.)
- 14) Osteoarthritis supplements such as glucosamine/chondroitin sulfate

Subject must stop participation in clinical trial when requiring use of restricted drugs for treatment during clinical trial period by decision of the investigator or

attending physician for treatment of other medical symptoms of the subject and its details must be recorded on the last page of case report.

## **7. EVALUATION VARIABLES AND PLAN FOR STATISTICAL ANALYSIS**

### **7.1 Evaluation Variables**

#### **7.1.1 Primary Effectiveness Evaluation Variables**

- Change in 100mm Pain VAS on 28th day compared to baseline

#### **7.1.2 Secondary Effectiveness Evaluation Variables**

- 1) Change in 100mm Pain VAS on 14th day compared to baseline
- 2) Change in K-WOMAC scale on 14th and 28th day compared to baseline
- 3) Patient Global Assessment
- 4) Frequency of rescue drug usage

#### **7.1.3 Safety Evaluation Variables**

- 1) Adverse reactions
- 2) Vital signs
- 3) Lab tests
- 4) Physical examination

### **7.2 Plan for Statistical Analysis**

#### **7.2.1 Definition of Analysis Sets**

Analysis sets are defined as below.

- (1) Safety analysis set: It consists of randomly assigned subjects who have been medicated with investigational products at least once.
- (2) FAS (Full Analysis Set): It consists of subjects that yield data on primary effectiveness evaluation variables who have been medicated with investigational products at least once.
- (3) PPS (Per-Protocol Set): It consists of subjects who completed the trial according to the clinical trial plan among subjects included in the FAS.

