#### **4.2.4 Visit 4(End of Clinical Trial, Day 28±3)**

This visit takes place on the last day of the study for final effectiveness evaluation of subjects administered investigational products for 28 days. Also, the following items are evaluated even if the clinical trial ends prematurely.

- 1) Check for changes in co-administered drugs compared to previous visit.
- 2) Investigate for occurrence of adverse events and its details.
- 3) Measure vital signs and weight and conduct physical examination.
- 4) Conduct laboratory tests(Hematologic test, blood chemistry test, urine test).
- 5) Conduct pregnancy test for female subjects of childbearing age.
- 6) Perform ECG.
- 7) Evaluate 100mm Pain VAS.
- 8) Evaluate K-WOMAC.
- 9) Evaluate Patient Global Assessment.
- 10) Recover residual clinical trials from the subject and record residual quantity.

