#### **7.2.2 General Statistical Principles**

Verification of all statistical significance shall be performed by a two-tail test

with significance level( $\alpha$ ) of 5%. However, noninferiority will be verified using the confidence interval.

Main analysis of data regarding effectiveness from subjects of this clinical trial shall be performed through PPS followed by additional analysis of FAS by principle.

Analysis of data regarding safety shall be performed through the safety analysis set.

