#### **7.2.6 Processing of Dropout or Missing Values**

The most recent data will be used for data analysis as if it was obtained at the corresponding point in time(Last Observation Carried Forward Method) should the subject is disqualified due to dropout or there is a missing value in data during FAS analysis before the clinical trial ends.

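### Read literally, the FAS excludes the dropouts to whom the plan applies LOCF, so the non-inferiority claim can rest on completers with no full-set check

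*Protocol*

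**What the plan says.** Protocol 7.2.1 defines the FAS: "It consists of subjects that yield data on primary effectiveness evaluation variables who have been medicated with investigational products at least once". Section 7.1.1 lists one primary variable: "Change in 100mm Pain VAS on 28th day compared to baseline". The Day 14 change is listed separately, as secondary, in 7.1.2.

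For dropouts and missing values in the FAS analysis, 7.2.6 prescribes LOCF: "The most recent data will be used for data analysis as if it was obtained at the corresponding point in time".

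The PPS is nested in the FAS: "It consists of subjects who completed the trial according to the clinical trial plan among subjects included in the FAS". Section 7.2.2 makes it the main set: the effectiveness analysis "shall be performed through PPS followed by additional analysis of FAS by principle". Section 5.4 lists use of prohibited co-medication as a critical violation. Its wording is awkward, but the next paragraph shows that such subjects are meant to leave the PPS. Section 6.7.2 counts analgesics other than the rescue drug as prohibited.

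Section 7.2.4.1 declares non-inferiority if the upper limit of the 95% interval is below 15 mm. It does not say in which analysis set.

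**The concern.** An FAS that requires the Day 28 value is a completer set. LOCF then has nobody to act on for the primary endpoint, and the FAS loses the same dropouts as the PPS. If LOCF is what the authors intended, the membership rule is wrong as written. An early VAS is then entered as though it were a Day 28 observation.

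This matters more in a non-inferiority trial than in a superiority trial. If poor outcomes are lost more often from the test arm, or if early values that show little difference are carried forward, the estimated difference shrinks and the claim becomes easier to make. The full set is the usual check on the per-protocol result. Here its membership is unclear and it has no stated part in the decision.

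**Working it through.** **The plan's own figure.** Section 3.2.2 gives a one-sided alpha of 0.025, power 0.975, SD 24.86 mm, margin 15 mm and dropout 10%.

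- n per group = 2 × 24.86² × (1.96 + 1.96)² / 15² = 84.41, rounded up to 85.
- 85 / 0.9 = 94.4, rounded up to 95.

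Both match the protocol. At 10% dropout, 19 of 190 subjects are at issue.

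**The passages side by side.**

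| Reading of the FAS | Dropouts in FAS | Role of LOCF for the primary | Dropouts in PPS |
|---|---|---|---|
| Needs a Day 28 value (7.2.1 with 7.1.1) | none; FAS about 171 | nothing to act on | none |
| Any post-baseline VAS is enough (implied by 7.2.6) | up to 19 | early value stands as Day 28 | none |

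The main set omits dropouts under either reading.

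**Completer bias (first reading).** Let d be the dropout proportion in each arm and g the amount by which dropouts do worse than completers, taken as equal in both arms. Each all-randomised mean is the completer mean plus d × g. The completer difference is therefore smaller than the all-randomised difference by (d_test − d_control) × g.

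The SE is 24.86 × √(1/n_t + 1/n_c), with n = 95 × (1 − d). At an all-randomised difference of exactly 15 mm, the one-sided error is Φ(−1.96 + shift/SE).

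The protocol gives neither g nor the split by arm, so both are assumed. The values of g are the cited trial's mean change of 18.34 mm (dropouts gain nothing), half of it (9.17 mm), and one SD (24.86 mm).

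| Dropout, test / control | g (mm) | Shift (mm) | SE (mm) | One-sided error |
|---|---|---|---|---|
| 10% / 10% | any | 0 | 3.80 | 2.5% |
| 15% / 5% | 9.17 | 0.10 × 9.17 = 0.92 | 3.81 | 4.3% |
| 15% / 5% | 18.34 | 0.10 × 18.34 = 1.83 | 3.81 | 7.0% |
| 15% / 5% | 24.86 | 0.10 × 24.86 = 2.49 | 3.81 | 9.6% |

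**LOCF dilution (second reading).** Take 10% dropout in each arm, 95 per arm analysed, SE = 24.86 × √(2/95) = 3.607, and a true Day 28 difference of 15 mm.

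- Carried values show half the difference (assumed): 0.9 × 15 + 0.1 × 7.5 = 14.25 mm. Error = Φ(−1.96 + 0.75/3.607) = Φ(−1.752) = 4.0%.
- Carried values show no difference (assumed): 0.9 × 15 = 13.5 mm. Error = Φ(−1.96 + 1.5/3.607) = Φ(−1.544) = 6.1%.

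The two calculations belong to different readings and must not be added together.

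**The case against.** The strongest reply is that 7.2.1 names no visit day and that 7.2.6 itself treats dropouts as FAS members. Pain VAS is measured at Day 14. Section 4.2.4 says that "the following items are evaluated even if the clinical trial ends prematurely", and 5.3 asks for a last visit. On that reading a dropout with any post-baseline VAS enters the FAS. This is a fair account of the probable intent, and it is why the exclusion holds only on a literal reading. It does not settle the matter: the definition still has to be rewritten to say so, the PPS still omits every dropout, and the FAS still has no stated role in the claim.

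Three stronger readings are tempting, and the protocol does not support them.

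- A reader might infer from 6.7.2 that subjects whose knee pain is not relieved must leave: "Subject must stop participation in clinical trial when requiring use of restricted drugs for treatment during clinical trial period". The sentence goes on to limit this to drugs needed, in a physician's judgement, for the subject's other medical complaints. Rescue acetaminophen is provided for pain, and the list in 5.3 has no explicit lack-of-efficacy item. Section 5.4 does remove users of prohibited analgesics from the PPS, but not from the FAS.
- A reader might infer that treatment failures necessarily vanish from both sets. Those who stay to Day 28 are in the FAS, and in the PPS if they kept to the plan.
- A reader might assume that the lost subjects are exactly the worst outcomes in each arm. At 15% versus 5% that gives about 4.1 mm and 19% error, but nothing in the protocol supports so extreme a pattern.

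The direction of bias is not fixed either. More control-arm dropout reverses the completer bias, and poor scores carried forward count against the arm with more failures.

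Finally, the choice of missing-data model and a joint decision rule may sit in a SAP that is not shown. Their absence here is not the defect. The defect is that two protocol sections conflict and that the protocol makes a completer set the main one.

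**Conclusion.** The point holds in limited form. Sections 7.2.1 and 7.2.6 contradict each other for the primary endpoint if the FAS definition is taken at its word. As written, the sole confirmatory claim can rest on completers without an effective full-set check.

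No particular bias is shown. The completer figures need unequal dropout, and the LOCF figures need carried values that understate the difference; the protocol gives no data on either. All the figures use the planning SD without baseline adjustment. If the planned covariance analysis reduces the SE, a given shift would raise the error somewhat more.

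The contradiction should be resolved before unblinding, because choosing the reading afterwards could affect the result.

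**What to change.** 1. In 7.2.1, define the FAS as all randomised subjects who took at least one dose, analysed as randomised, with no Day 28 requirement. In practice those who contribute have a baseline and at least one post-baseline Pain VAS, including early-termination values. State how dosed subjects with no post-baseline VAS are handled, since no outcome model can recover them. Bring 7.2.6 into line.
2. For the FAS primary analysis, replace LOCF with a mixed model for repeated measures on the Day 14 and Day 28 changes, with baseline VAS, treatment, visit and treatment-by-visit. Add a sensitivity analysis that penalises missing test-arm values by amounts up to the margin.
3. In 7.2.4.1, declare non-inferiority only if the upper limit is below 15 mm in both the PPS and the FAS.

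The cost is revised wording, a little more programming and a small loss of power. With a true difference of zero and only 85 per group in each set, power is 97.6% in each, so the chance of passing both is at least 1 − 2 × 0.024 = 95.2%. The sample size of 85 evaluable and 95 randomised per group does not change.

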#### **7.2.2 General Statistical Principles**

Verification of all statistical significance shall be performed by a two-tail test

with significance level( $\alpha$ ) of 5%. However, noninferiority will be verified using the confidence interval.

Main analysis of data regarding effectiveness from subjects of this clinical trial shall be performed through PPS followed by additional analysis of FAS by principle.

Analysis of data regarding safety shall be performed through the safety analysis set.

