#### **5.4 Clinical Trial Compliance and Action for Plan Violation**

Supervisor and instructor for this clinical trial shall understand and strictly perform the clinical trial according to the plan to prevent violations of clinical trial plan. The clinical trial supervisor shall conduct telephone monitoring and send out written notifications regarding future visiting hours as well as taking appropriate action for subjects for visitation for compliance with clinical trial administration and examination schedule. Violations of clinical trial plan which occur despite such efforts will be processed as below.

Critical violations of clinical trial plan will result in disqualification of corresponding subject from analysis(Excluding PPS) by principle and the conditions are as listed below.

- ① Lack of consent form
- ② Violation of inclusion/exclusion criteria
- ③ Administered with prohibited co-administered drugs during clinical trial period
- ④ Omission of major examination in the trial period

Other minor violations of clinical trial plan that are deemed to not affect other matters and interpretation of study results will be included in the PPS analysis after overall observation whether such violations have impacted the study

conducted by the investigator, client, monitor, and statistician when writing the conclusion report by listing the exact details and reason of violation or delay.

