#### **7.2.4.1 Primary Effectiveness Analysis**

- Change in 100mm Pain VAS on 28th day compared to baseline

Calculate the upper limit(97.5% one-sided confidence interval) for 95% two-sided confidence interval for the difference in change of 100mm Pain VAS on the 28th day compared to baseline of test and control groups(Average change in test group - Average change in control group). If the upper limit of the confidence interval is below 15mm, then it shall be determined that the test group is not inferior compared to the control group. For this, configure the change in 100mm Pain VAS as dependent variable with the administration group as the random factor, and the baseline 100mm Pain VAS as the covariate to perform the covariance analysis. Suggest the calibrated average for the change in 100mm Pain VAS for each administration group based on this analysis and suggest the difference in calibrated means between the two group and its 95% confidence interval.

Additionally, mean, standard deviation, minimum and maximum values shall be suggested for the amount of 100mm Pain VAS measured at each visit for the test group and the control group and the change in 100mm Pain VAS on the 28th day compared to baseline.

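### As written, the per-protocol interval alone decides non-inferiority; requiring the full analysis set to agree is a cheap improvement, though not a guarantee of 2.5% error

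*Protocol*

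**What the plan says.** Protocol section 7.2.2 ranks the two effectiveness sets: the main analysis "shall be performed through PPS followed by additional analysis of FAS by principle". Section 7.2.4.1 gives the decision rule: "If the upper limit of the confidence interval is below 15mm, then it shall be determined that the test group is not inferior". That sentence names no analysis set and attaches no condition on the FAS. No section says what follows if the two sets disagree.

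Section 7.2.1 defines the FAS ("It consists of subjects that yield data on primary effectiveness evaluation variables who have been medicated with investigational products at least once") and the PPS as a subset of it ("It consists of subjects who completed the trial according to the clinical trial plan among subjects included in the FAS").

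Three provisions bear on who leaves the PPS:
- Section 5.4 lists as a critical violation "Administered with prohibited co-administered drugs during clinical trial period". The translated sentence on what a critical violation leads to is garbled. Since minor violators are the ones who may stay in the PPS, the sense must be that critical violators leave it.
- Section 6.7.2 restricts pain relievers other than the rescue drug and adds: "Subject must stop participation in clinical trial when requiring use of restricted drugs for treatment during clinical trial period".
- Section 5.4 has minor violations judged in a review "conducted by the investigator, client, monitor, and statistician when writing the conclusion report".

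For subjects who leave early, section 4.2.4 schedules a final VAS, and section 7.2.6 fills gaps in the FAS by last observation carried forward (LOCF).

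**The concern.** PPS membership is settled after randomisation and can depend on how the subject fared. A subject whose pain is not controlled is more likely to take, or to need, a prohibited analgesic, and so to leave the PPS. If the test drug is truly worse, it has more such subjects. The same exclusion rule, applied evenly to both arms, then removes more failures from the test arm and shrinks the PPS difference. That favours a non-inferiority claim.

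The FAS is the natural check on this, because it keeps those subjects. Under the plan it is computed but has no part in the decision. At stake is the one-sided 2.5% error rate stated in section 3.2.2.

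**Working it through.** **Inputs.** From section 3.2.2: margin 15 mm, SD 24.86 mm in each arm, control change -18.34 mm, one-sided alpha 0.025, power 0.975, dropout 10%, 85 evaluable and 95 enrolled per group. Assumed here, not in the protocol: a true difference of exactly 15 mm; removal from the PPS limited to subjects with a change above 0 (no improvement), at the same probability in both arms; unadjusted two-sample t limits, because the protocol gives no baseline correlation for the planned covariance analysis.

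**1. The plan's own sample size.** n = 2 × 24.86² × (1.96 + 1.96)² / 15² = 84.4, so 85 per group; 85 / 0.9 = 94.4, so 95. Both figures reproduce.

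**2. Who can be removed.** The test mean is -18.34 + 15 = -3.34 mm.
- Test arm: P(change > 0) = 1 − Φ(3.34/24.86) = 1 − Φ(0.134) = 44.7%.
- Control arm: 1 − Φ(18.34/24.86) = 1 − Φ(0.738) = 23.0%.

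If 30% of non-improvers leave, the loss is 0.3 × 44.7 = 13.4% and 0.3 × 23.0 = 6.9%, an average of about 10%, which is the planned rate.

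**3. False non-inferiority from the PPS alone** (simulation, 95 per arm, tens of thousands of trials per row).

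| Non-improvers leaving | Loss test / control | Average loss | Mean PPS difference | PPS-only error |
|---|---|---|---|---|
| Random loss, 10% | 10% / 10% | 10% | 15.0 mm | about 2.5% |
| 20% | 8.9% / 4.6% | about 7% | 14.4 mm | about 3.5% |
| 30% | 13.4% / 6.9% | about 10% | 14.0 mm | about 4.5% |
| 60% | 26.8% / 13.8% | about 20% | 12.2 mm | about 12% |

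Hand check of the 30% row: about 82 and 88 subjects remain, so SE ≈ 24.86 × √(1/82 + 1/88) = 3.8 mm. The PPS difference is about 1.0 mm below the margin, and Φ(1.0/3.8 − 1.96) = Φ(−1.70) ≈ 4.5%.

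**4. Requiring both sets, at about 10% average loss.** The answer depends on what the FAS holds for the subjects removed from the PPS.

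| FAS value for removed subjects | Error, both sets required |
|---|---|
| True day-28 or early-termination VAS | about 2.2% |
| Half of the true change captured | about 3% |
| Baseline carried forward (change = 0) | about 4.4% |

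A repeat run of steps 3 and 4 agreed to within about half a point at 20% loss and about 0.2 point elsewhere; it gave 2.0%, 3.2% and 4.2% for the three rows of step 4.

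**5. Power cost.** At a true difference of 0 with 10% random loss, power is about 97.5% for the PPS alone and about 97.2 to 97.3% when both sets must pass.

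**6. When the drugs are equal.** At a true difference of 0 the same removal rule takes equal shares from each arm and leaves the mean difference at about 0. The effect arises only when the test drug is truly worse.

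**The case against.** The strongest case against has four parts.

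- **No sentence says that the PPS alone decides.** The 15 mm rule names no set, the FAS analysis is planned and would be seen, and a statistical analysis plan not shown here might say how disagreement is handled. This stands as a caution. But the protocol itself fixes one set as main and the other as additional, and makes the conclusion follow from one limit; a later concordance rule would change that decision rule.
- **A PPS main analysis is a legitimate choice in a non-inferiority trial.** This stands. A reader might infer that the choice of the PPS is itself the error; the documents do not support that. The weakness is only that the FAS has no say.
- **The removal model has thin support.** Lack of relief is not a listed stopping reason in section 5.3, and section 6.7.1 permits rescue acetaminophen, so poor relief alone breaks no rule. Prohibited analgesics are the clearest pain-related route, and withdrawal of consent could be another. Nothing in the protocol says how many non-improvers would leave. This stands, and it is why the size is given as a range that starts at no inflation.
- **The FAS may not protect.** If early leavers enter with baseline carried forward, requiring both sets gains almost nothing (about 4.4% against 4.5%). That is the unfavourable extreme, since section 4.2.4 asks for a final VAS on early termination. It still rules out any promise that the fix restores 2.5%.

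A reader might also infer from the timing of the minor-violation review that PPS membership is settled with treatment codes open. The protocol does not say so; it only omits to say that the review comes before unblinding.

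**Conclusion.** The point holds as a cheap improvement. Sections 7.2.2 and 7.2.4.1 together let the PPS interval decide, and a failing FAS would not stop the claim. At the planned 10% average loss, with every lost subject a non-improver, a true difference of 15 mm and unadjusted t limits, the error is about 4.5% rather than 2.5%.

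Two stronger readings are not supported. An error of about 12% needs about 20% average loss, twice the planned rate. Higher figures still can be obtained by assuming outcome-related removal in the test arm only or near-complete removal of the worst outcomes; no section suggests either. Nor is the 2.5% rate lost whenever exit relates to pain: the effect needs removal that takes more poor outcomes from a truly worse test arm, and random loss leaves the error at about 2.5%.

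The planned baseline-adjusted analysis would change these figures somewhat; the protocol gives no correlation from which to say by how much.

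**What to change.** In sections 7.2.2 and 7.2.4.1, state that non-inferiority is concluded only if the upper limit of the 95% confidence interval is below 15 mm in both the PPS and the FAS, and that it is not concluded if the two sets disagree.

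A claim that must pass both tests can never be made more often than one that must pass the PPS test alone, so the change cannot add false claims. How far it lowers the error depends on how completely the final VAS is obtained from early leavers, so it should be presented as reducing the risk and not as securing 2.5%.

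The cost is two sentences and about 0.2 to 0.3 point of power at a true difference of 0 with 10% random loss. Power stays close to the planned 97.5%, so 85 evaluable and 95 enrolled per group can stand. No new data or subjects are needed.
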